## Results

For this study, funding has already been awarded and enrollment has been completed. Data are currently being evaluated.

## Discussion

### Summary

This cross-sectional study was designed to evaluate work ability in a population of seropositive RA patients and its association with RA disease activity, muscle strength functional disability, lower extremity function, and frailty. This study will also assess the quality of sleep and sexual functioning in RA and the respective association of these factors with disease activity.

### Implications for Research and Clinical Practice

On the basis of the large number of people affected, RA not only lowers patients’ quality of life but also poses an economic burden to both patients and society in general [55]. The direct health care–related costs of RA are dominated by in-patient care, but the total costs are found to be mainly related to work disability and temporary or permanent loss of work [55,56].

This study will allow the estimation of the rates of RA patients at risk for incapacity for work and will evaluate the association of work disability with modifiable parameters such as muscle strength and functional ability, which has not been investigated in RA before. It will provide further insights into work ability in RA and its associated risk factors. Any evidence of association may motivate further research, and the findings might encourage interventions focused specifically on improving muscle strength and lower extremity function to positively affect work ability. The outcomes of this study may also motivate clinicians to screen for work ability and modifiable parameters in the RA population.

Aside from work ability, quality of sleep and good sexual functioning beneficially affect one’s quality of life [57]. This study will provide insights into the rates of RA patients with impaired sleep and sexual dysfunction and the association of these functions with RA disease activity. The findings may encourage future research and interventions for the improvement of RA-associated problems, which tend to be poorly addressed in routine care. A screening tool for sexual functioning in RA patients was used in this study, and the applicability of the tool will be evaluated.

### Strengths and Limitations

The study is limited by its cross-sectional design, which allows us to draw a conclusion about association but not causality. However, as we intend to analyze multiple outcomes and potential risk factors, we considered this approach to be ideal for generating hypotheses for further interventional approaches or longitudinal studies. Another potential limitation might be the pain-related noncompliance of patients during physical measurements. High disease activity and pain may possibly lead to some degree of bias in the results.

An advantage of this study is the availability of patients from various settings. Through recruitment at an outpatient clinic and a day clinic, the whole spectrum of different disease activities can be investigated. All study-related measures can be performed in short time periods without the necessity of a second appointment, thereby assuring high patient compliance and a marginally low drop-out rate.

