### Rheumatoid Arthritis and Work Ability

Chronic diseases such as RA are negatively associated with work ability. Work ability, as described by Ilmarinen from the Finnish Institute of Occupational Health, is the interaction of individual determinants (health, competence, and attitudes) and the work environment [3]. It is determined by an individual’s perception of the demands at work and the ability to cope with them [4]. Although RA-induced work disability rates seem to decrease because of new therapeutic concepts, RA is still a fundamental burden for many patients [5]. The costs of work disability in rheumatic conditions are high, generally higher than the treatment costs [6]. Furthermore, from the patients’ perspective, work disability significantly affects their basic income [7].

Work disability in RA appears to be multifactorial; symptoms such as pain, swelling, and stiffness play a major role, as they directly affect functional disability [8]. RA is associated with loss of muscle mass and diminished strength. In healthy individuals, only a weak association between muscle strength and workability could be found [9]. The influence of strength on the work ability of RA patients has yet to be determined.

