### Data Collection and Procedures

Demographic, clinical data, and disease activity will be assessed through clinical examination and administration of an interview questionnaire. The demographic characteristics include gender, age, marital status (married/common law, single/widowed/ divorced), highest level of education (compulsory schooling, secondary school graduation, higher education), and type of occupation.

Disease-specific clinical characteristics include disease duration (months) and current medication use for each of the following categories: analgesics/nonsteroidal anti-inflammatory drugs, disease-modifying antirheumatic drugs, biologic agents (biologicals), and drugs for other medical conditions.

Pain will be assessed via a visual analog scale (VAS), a unidimensional measure of pain intensity that has been widely used in diverse adult populations, including those with rheumatic diseases. The VAS consists of a 10 cm line anchored by verbal descriptors (1=no pain at all, 10=maximum pain) [34]. The patient will be asked to place a line perpendicular to the VAS line to indicate his or her current pain intensity.

Overall disease activity will be measured with the Clinical Disease Activity Index (CDAI). The CDAI is validated and widely used [35], with the scoring done as per the following formula: CDAI = SJC-28 + TJC-28 + PGA + EGA, where SJC-28 is the Swollen 28-Joint Count (shoulders, elbows, wrists, metacarpophalangeal joints, proximal interphalangeal joints including thumb interphalangeal joint, knees), TJC-28 is the Tender 28-Joint Count, PGA is the Patient Global Assessment (patient’s self-assessment of the overall RA disease activity on a scale of 1 to 10, where 10 is the maximal activity), and EGA is the Evaluator’s Global Assessment (evaluator’s assessment of the overall RA disease activity). As proposed by the American College of Rheumatology 2008, the CDAI score will be interpreted as follows: remission = CDAI ≤ 2.8, low disease activity = CDAI > 2.8 and ≤ 10, moderate disease activity = CDAI > 10 and ≤ 22, and high disease activity = CDAI > 22.

Laboratory assessments include CRP (mg/dL), IL-6 (pg/mL), and TNF-α (ng/mL). For the detection of IL-6 and TNF-α, high-sensitivity enzyme-linked immunosorbent assay will be used, assayed in duplicates. The CRP will be measured with the patients’ routine laboratory assessments. Blood samples will be analyzed at the Institute for Laboratory Medicine of the SMZ-Süd, Vienna, Austria.

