### Statistical Analysis

All statistical computations will be performed with SPSS version 22.0.2 (IBM Corp). The primary hypothesis of the study, “A difference in work ability and muscle strength exists in patients with high versus low disease activity,” will be tested with a Pearson chi-square test. For the descriptive statistics, mean values will be calculated for continuous variables, and categorical variables will be presented in percentages. Continuous parameters will be checked for normal distribution (Kolmogorov-Smirnov test, Levene test, histogram, and Q-Q plot check), and an unpaired Student *t* test will be performed, as appropriate. Otherwise, the Mann-Whitney U test will be used to identify differences between patients with high versus low disease activity. For categorical parameters, a Pearson chi-square test or Fisher exact test will be used if the cell count is <5. Binary logistic regression will be used to evaluate the impact of frailty, functional ability, and muscle strength on work ability. For metric data, Pearson correlation or Spearman rank correlation (given outliers or nonlinear but monotone associations) will be used to evaluate associations of interest. A *P* value of <.05 will be considered statistically significant for all tests.

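### The planned regression of work ability on muscle strength names neither pain nor disease activity, so a strength association may partly reflect pain-limited effort; fitting it with and without the recorded pain VAS would show how much

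*Protocol article*

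**What the plan says.** All references are to the protocol article.

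- **Strengths and Limitations** raises pain twice in succession: "Another potential limitation might be the pain-related noncompliance of patients during physical measurements", then "High disease activity and pain may possibly lead to some degree of bias in the results".
- **Rheumatoid Arthritis and Work Ability** calls work disability multifactorial and says that "symptoms such as pain, swelling, and stiffness play a major role, as they directly affect functional disability".
- **Data Collection and Procedures** records pain: "Pain will be assessed via a visual analog scale (VAS), a unidimensional measure of pain intensity". What is captured is pain at that moment: "The patient will be asked to place a line perpendicular to the VAS line to indicate his or her current pain intensity". The same section defines disease activity as "CDAI = SJC-28 + TJC-28 + PGA + EGA", which includes tender joints and the patient's global rating but not the pain VAS.
- **Muscular Strength Measurement** obtains both quadriceps and grip strength from maximal voluntary contractions.
- **Statistical Analysis** gives the model: "Binary logistic regression will be used to evaluate the impact of frailty, functional ability, and muscle strength on work ability". For metric data, Pearson or Spearman correlation "will be used to evaluate associations of interest". No partial correlation is mentioned, and the pain VAS has no role in any analysis that the section names.
- **Implications for Research and Clinical Practice** treats strength as modifiable and says the findings might encourage interventions aimed at it.

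**The concern.** A maximal voluntary contraction measures what the patient is willing and able to exert on the day. Pain can lower that reading without any change in the muscle, and the article also presents pain as a driver of work disability. Pain can therefore lower recorded strength and work ability together, and so produce an association between them even if strength has no effect of its own. A regression that contains strength but not pain cannot separate the two.

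At stake is how a secondary result is labelled. The article expects the strength finding to motivate further research and possibly strength-directed interventions. If part of the association is pain-limited effort, the hypothesis passed on is mislabelled, although a variable that would help to check it is already in the data set.

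**Working it through.** **The plan's own figure.** The plan gives no figure for this regression. Its only sample size, 71, belongs to the primary comparison. For 40% versus 80%, a 30:70 split, two-sided alpha .05 and 80% power, the recalculated total is about 53 without and 63 with continuity correction, so 71 is not reproduced (uncorrected power at 71 is about 0.91). That is a separate matter. Here 71 serves only as the plan's evaluable number, and 100 as its enrolled number.

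**Inputs from Sample Size.** Expected share with good work ability: 0.7 × 0.8 + 0.3 × 0.4 = 0.68. Patients without it at n = 71: 71 × 0.32 = 22.7, about 23. This treats everyone as high or low activity, as the sample-size calculation does.

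**Assumed inputs (none are in the documents).** Strength has no effect of its own on work ability.

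**Step 1: residual correlation after CDAI.** Let a = r(pain, strength), b = r(pain, work ability) and c = r(pain, CDAI), with strength, work ability and CDAI related only through pain. Then

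partial r(strength, work ability | CDAI) = ab(1 − c²) / √[(1 − a²c²)(1 − b²c²)].

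- a = −0.3, b = −0.4, c = 0.6: 0.12 × 0.64 / √(0.9676 × 0.9424) = 0.0768 / 0.955 = 0.08 (0.12 unadjusted).
- a = −0.5, b = −0.6, c = 0.4: 0.30 × 0.84 / √(0.96 × 0.9424) = 0.252 / 0.951 = 0.26 (0.30 unadjusted).

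The covariance left after CDAI is the fraction 1 − c²: 0.84, 0.64 and 0.36 at c = 0.4, 0.6 and 0.8. It falls below one half once c exceeds √0.5 ≈ 0.71.

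**Step 2: false-positive rate of the strength term.** Logistic regressions were simulated, 1,000 replicates per setting. Assumed log odds ratios on good work ability were −1.0 per SD of pain and −0.5 per SD of CDAI. Ranges run over r(pain, strength) from −0.3 to −0.5.

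| N | r(pain, CDAI) | Strength alone | + CDAI | + CDAI and VAS |
|---|---|---|---|---|
| 71 | 0.4 | 20-44% | 14-27% | 4-5% |
| 71 | 0.6 | 20-52% | 8-17% | 4% |
| 71 | 0.8 | 22-53% | 5-9% | 4% |
| 100 | 0.4 | 25-61% | 17-36% | 5-6% |
| 100 | 0.6 | 25-64% | 10-23% | 5-6% |
| 100 | 0.8 | 33-70% | 8-11% | 5-6% |

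The Monte Carlo standard error near 5% is √(0.05 × 0.95 / 1000) ≈ 0.7 points. At N = 71 the median odds ratio per SD of strength is 1.35-1.75 alone, 1.13-1.51 with CDAI, and 1.00-1.03 with CDAI and VAS; the true value is 1.

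**Control run.** With no pain-strength link, at N = 71 and r(pain, CDAI) = 0.6, the three rates are 5.6%, 6.2% and 6.1%. The excess therefore comes from the assumed link.

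**Limits of the check.** The strength-alone column also carries the assumed CDAI effect. The VAS was added together with CDAI; no run added it alone. Frailty and functional ability were not in the simulated model.

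**The case against.** The strongest case against is that this is one unlisted covariate in a condensed article. A full covariate list for a secondary regression may sit in a protocol or analysis plan that is not shown. That stands to this extent: one can say only that the analyses named here give pain no role, not that no analysis will use it. It does not remove the point, because the article does name this model's predictors, and it presents pain as a limitation without pointing to any analysis that addresses it.

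A reader might infer that the article admits that pain biases the strength tests. It does not. The wording is hedged and speaks of the results generally. The preceding sentence concerns noncompliance, which Sample Size also lists among the reasons for the 30% loss, so it may mean uncompleted tests rather than submaximal effort.

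A reader might also infer that most of the pain effect would survive adjustment for CDAI. No such adjustment is planned, and CDAI carries some pain through tender joints and the patient global rating. How much would survive depends on a correlation that the documents do not give; at 0.8, CDAI alone brings the rate close to nominal at N = 71.

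Two further objections stand. If functional ability enters the same model, it would absorb part of the pain pathway, so the simulated strength-alone rates may overstate the problem. And the VAS records current pain, not pain during the contraction, so it is an imperfect check.

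**Conclusion.** The point holds in a limited form. The article flags pain as a possible source of bias in connection with physical measurements, links pain to work disability and records it, but names neither pain nor CDAI in the strength regression. An apparent strength association may therefore partly reflect pain-limited effort. With no true strength effect and N = 71, the false-positive rate is about 20-53% for strength alone, 5-27% with CDAI added, and 4-5% with CDAI and the VAS. These sizes rest entirely on assumed correlations and effect sizes; they show that the mechanism can matter, not that it does in these data.

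It would go too far to say that a strength-based conclusion would be wrong, or that only a pain-adjusted coefficient may support one. The article limits itself to association and hypothesis generation, and says only that findings might encourage interventions. Pain may also partly result from weakness: Rheumatoid Arthritis and Muscle Strength reports that hand exercise can reduce pain as well as raise strength. Adjusting for pain could then remove part of a real strength association. Severity is low: a secondary objective and an inexpensive companion analysis.

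**What to change.** Under Statistical Analysis, pre-specify the regression of work ability on muscle strength (grip and quadriceps) in two forms that are otherwise identical, one without and one with the pain VAS as a covariate. Report both strength coefficients with their intervals. If CDAI is also adjusted for, include it in both forms. Describe strength as a possible intervention target only in light of both coefficients, and state two cautions: the VAS measures current pain rather than pain during the test, and pain may partly follow from weakness.

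The change affects analysis wording only. Enrollment is complete and the VAS is already collected, but the data are being evaluated, so the pair of models should be fixed before the strength results are examined, or else labelled as added later. The cost is one more coefficient and a somewhat wider interval for strength. With about 23 patients lacking good work ability at n = 71, going from three coefficients (one each for frailty, functional ability and strength) to four lowers the number of such patients per coefficient from 23 / 3 ≈ 7.7 to 23 / 4 ≈ 5.8. That is a reason to keep the rest of the model small.

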## Abbreviations

CDAI: Clinical Disease Activity Index
CRP: C-reactive protein
EGA: Evaluator’s Global Assessment
HAQ-DI: Health Assessment Questionnaire Disability Index
IL: interleukin
MOS-SS: Medical Outcomes Study Sleep Scale
PGA: Patient Global Assessment
RA: rheumatoid arthritis
SHARE-FI: Survey of Health, Ageing and Retirement in Europe–Frailty Instrument
SJC-28: Swollen 28-Joint Count
SMZ: Sozialmedizinisches Zentrum
SPPB: Short Physical Performance Battery
TJC-28: Tender 28-Joint Count
TNF-α: tumor necrosis factor-α
VAS: visual analog scale
WAI: Work Ability Index
WAS: Work Ability Score
